## Abstract

**Background:**

International medical organizations such as the American Society of Medical Oncology recommend early palliative care as the “gold standard” for palliative care in patients with advanced cancer. Nevertheless, even in Comprehensive Cancer Centers, early palliative care is not yet routine practice. The main goal of the EVI project is to evaluate whether early palliative care can be implemented—in the sense of “putting evidence into practice”—into the everyday clinical practice of Comprehensive Cancer Centers. In addition, we are interested in (1) describing the type of support that patients would like from palliative care, (2) gaining information about the effect of palliative care on patients’ quality of life, and (3) understanding the economic burden of palliative care on patients and their families.

**Methods/design:**

The EVI project is a multi-center, prospective cohort study with a sequential control group design. The study is a project of the Palliative Care Center of Excellence (KOMPACT) in Baden-Württemberg, Germany, which was recently established to combine the expertise of five academic, specialist palliative care departments. The study is divided into two phases: preliminary phase (months 1–9) and main study phase (months 10–18). In each of all five participating academic Comprehensive Cancer Centers, an experienced palliative care physician will be hired for 18 months. During the preliminary phase, the physician will be allowed time to establish the necessary structures for early palliative care within the Comprehensive Cancer Center. In the main study phase, patients with metastatic cancer will be offered a consultation with the palliative care physician within eight weeks of diagnosis. After the initial consultation, follow-up consultations will be offered as needed. The study is built upon a convergent parallel design. In the quantitative arm, patients will be surveyed in both the preliminary and main study phase at three points in time (baseline, 12 weeks, 24 weeks). Standardized questionnaires will be used to measure patients’ quality of life, symptom burden and mood. Using interviews with palliative care physicians, oncologists, department heads, patients and their caregivers, the qualitative arm will explore (1) what factors encourage and hinder the early integration of palliative care into standard oncology care, (2) what support patients and their caregivers would like from palliative care, and (3) what effect palliative care has on the economic disease burden of patients and their families.

**Discussion:**

The study proposed is meant to serve as a catalyzer. Local palliative care teams should be put in position to routinely cooperate with the primary treating department at their respective cancer center. The long-term goal of this project is to create sustainable improvements in the care of patients with incurable cancer.

**Trial registration:**

DRKS00006162; date of registration: 19/05/2014

## Background

The primary goal of palliative care (PC) is to ensure quality of life (QoL) for patients with incurable, life-limiting diseases and their caregivers. This is true for all patients, regardless of their disease (e.g. amyotrophic lateral sclerosis, multiple sclerosis, heart failure, chronic obstructive pulmonary disorder, etc.) However, patients with incurable cancer remain one of the largest patient groups with a need for palliative care [1]. Due to the continuing advances in cancer treatment, cancer is likely to increasingly become a chronic disease [2].

In the past and even today, PC has often been falsely equated with end-of-life care [3]. For this reason, treatment goals in standard oncology care have often focused solely on prolonging life rather than improving QoL early in the course of the disease [4]. Even in early stages of the disease, patients with incurable cancer often suffer from multiple physically burdensome symptoms (e.g. pain) [5] and psychosocial and spiritual anxiety. By focusing on life-prolonging treatment options, the suffering that patients and their families experience from these symptoms often goes unnoticed and is not adequately relieved [3]. The outdated dictum “first prolong life, then improve quality of life” should be replaced by a holistic, integrative model [6]. This approach is referred to as early palliative care (EPC). According to this model, specialist palliative care expertise focused on the needs of the patient should be offered alongside standard oncology care [7].

For patients with non-small cell lung cancer (NSCLC), Temel et al. [8] showed that EPC improved patients’ QoL, reduced the incidence of depression, and decreased the number of aggressive (and generally futile) therapies at the end of life. In addition, EPC increased patients’ survival time [8]. In a randomized study with patients suffering from different cancer entities, Zimmermann et al. [9] found that patients who received EPC not only had a better QoL but also a higher level of satisfaction with their treatment compared to those in the control group, who were not offered EPC.

Meanwhile, international medical organizations such as the American Society of Medical Oncology (ASCO) have recommended EPC as the “gold standard” for palliative care in patients with advanced cancer [3]. However, integrating palliative care into standard oncology care early in the course of the disease requires a reorientation and restructuring of current medical practice. For this reason, EPC has not yet become a routine part of care even in Comprehensive Cancer Centers (CCCs) [3].

In spite of their clear recommendation for EPC, the National Cancer Institute and the ASCO also point out that there are considerable deficits in the currently available publications on EPC [3]. These institutions criticize that studies have focused on limited patient populations (e.g. patients with NSCLC) rather than the entire spectrum of cancer patients who are actually treated in CCCs. Furthermore, recent studies have been criticized because they have been conducted under ideal circumstances, which do not correspond to the real-life situation. This makes it impossible to assess the feasibility and effectiveness of EPC in the actual clinical setting [10]. Until now, there has been a lack of research investigating the implementation of EPC into everyday clinical practice, using the already available resources and structures [11]. In light of this, the study proposed here aims to implement EPC into clinical practice at all five CCCs throughout the federal state of Baden-Württemberg, Germany. The study is a project of the Palliative Care Center of Excellence (KOMPACT) in Baden-Württemberg, Germany. It is funded by the Robert Bosch Foundation who has formally peer reviewed our study protocol before assigning the grant. Patients with advanced metastatic cancer that is unresponsive to curative treatments will routinely be offered palliative care as soon as possible after diagnosis, according to the most up-to-date international treatment standards.

The main goal of the EVI project is to evaluate whether EPC can be implemented into the everyday clinical practice of CCCs, and if so, what conditions are necessary for it to succeed. In addition, we are interested in (1) describing the type of support that patients would like from palliative care, (2) gaining information about the effect of palliative care on patients’ QoL and healthcare costs, and (3) determining which factors could potentially encourage or hinder the implementation of EPC, respectively.

## Methods/design

### The design of the study

In the field of PC, conducting clinical studies is associated with considerable challenges. Reasons for this include (1) a lack of established scientific standards for PC research questions and (2) the complex medical and personal situation of PC patients, which places unique demands on the design of studies with this patient population [12]. Only recently was a guidance statement for end-of-life care research developed in the context of the “Methods of Researching End of Life Care” (MOREcare) project, which expanded on the Medical Research Council guidance on the development and evaluation of complex circumstances [13]. The design of the study proposed here closely follows the guidelines established by the MOREcare project. Another important underlying premise of our project is its real-world design, which involves the routine implementation of EPC in the clinical setting and helps avoid artificial study conditions.

The study is divided into two phases: preliminary phase (months 1–9) and main study phase (months 10–18). In each of the five participating CCCs, an experienced palliative care physician will be hired for 18 months with a 50 % position. During the preliminary phase of the study, the physician will be allowed time to establish the necessary structures for EPC within the clinic. In addition, patients will also be recruited during this phase to establish a reference group for comparison between the status quo and those in the main study phase who receive EPC.

In the main study phase, patients with metastatic cancer will routinely be offered a consultation with the PC physician within eight weeks of diagnosis. This initial consultation has multiple objectives. First, this meeting serves to provide information regarding the value and accessibility of specialist palliative care. The PC physician will explain to patients that interdisciplinary cancer treatment ensures that all meaningful treatment options will continue to be available (“fight against cancer”) but that high priority will be placed on QoL also. For QoL needs, specialist palliative care services will be available to patients alongside treatment from the primary cancer specialist. It is important to make clear to patients that EPC is supplementary to standard oncology care and aims at supporting the treating cancer specialist. The cancer specialist will remain the primary contact person regarding patients’ treatment options.

The second main objective of the initial consultation is to create a certain familiarity with palliative care, which will help reduce barriers to accessing these services in the future.

In the initial consultation, a detailed assessment of patients’ physical symptoms (e.g. pain), psychosocial issues, spiritual burden and information needs will be conducted using a combination of both structured and unstructured methods. If an intervention appears necessary (e.g. adjusting medications), suggestions will be provided to the primary treating physician and, when possible, will be carried out directly in the outpatient clinic of the CCC. In these cases, a follow-up consultation will be arranged between the patient and PC physician. Otherwise, patients and treating physicians have the possibility to contact the PC physician as necessary. Follow-up consultations are therefore not obligatory. Rather, additional meetings will take place as needed, according to the requests of patients, family members/caregivers or the treating physician.

In order to ensure that the EPC services in all five CCCs are comparable, the palliative care physicians will receive a special structured training during the preliminary phase of the study. In an earlier project, a leading researcher from our working group established which factors are important for the early implementation of palliative care [7]. Based on this, a method was developed to improve physicians understanding of the initial PC consultation and cooperation between various medical specialties [14]. This method will serve as the basis of our training for PC physicians in this study.

Before the main study phase begins, cancer specialists at each center will be comprehensively informed about the possibilities of EPC so that they are able to prepare patients for the PC consultation. We will spread information about EPC by distributing informational brochures, sending a regular newsletter to physicians and nurses, and by holding presentations to the tumor boards of each participating center.

To evaluate the feasibility of the routine implementation of EPC in CCCs, the study is built upon a convergent parallel design [15]. The quantitative arm is conceived as a multi-center, prospective cohort study with a sequential control group design. Both in the preliminary and main study phase, patients will be surveyed at three points in time (baseline, 12 weeks, 24 weeks). Standardized questionnaires will be used to measure patients’ QoL, symptom burden and mood. The economic effects of EPC will be measured using an expense log or cost diary.

In light of the objective to test the feasibility of EPC, the qualitative arm of the study consist of four interview studies with palliative care physicians, oncologists/department heads, patients and their families/caregivers. These interviews will explore: (1) which factors encourage and hinder the early integration of palliative care into standard oncology care and (2) what support patients and their families would like from palliative care and to what extent these needs can be met through the EPC approach used in this study.

After conclusion of the study, the results of the quantitative and qualitative arms will be synthesized and evaluated with regard to the feasibility of EPC in CCCs.

### Quantitative arm

#### Participants

The EPC services provided in this study are aimed at patients with advanced metastatic cancer that is unresponsive to curative treatments (ICD 10 C 1–80 plus ICD 10 C 78–79). In all participating CCCs, patients will be identified in the tumor boards of each center. As soon as the diagnostic process has been concluded and treatment has started (i.e. within the first eight weeks after diagnosis), patients will be referred to the PC physician. Table 1 shows the inclusion and exclusion criteria for participation.

**Table 1 Tab1:** Inclusion and exclusion criteria for participation in the quantitative study arm

Inclusion criteria:	
1.	Initial diagnosis of a metastatic, incurable cancer (ICD 10 C 1–80 plus ICD 10 C 78–79) occurred within the last eight weeks, particularly:
	- non-small cell lung cancer (NSCLC) without epidermal growth factor (EFGR) mutations: met. NSCLC Stage IV – ICD C34.[01239] + metastasis code or C34.8 (multiple subdomains) + possibly M8012/3 (large cell carcinoma)
	- met. esophageal carcinoma Stage IV – ICD C15.[123459] + metastasis code or C15.8 (multiple subdomains) + possibly M8070/3 (squamous cell carcinoma)
	- met. stomach carcinoma Stage IV - ICD C16.[01234569] + metastasis code or C16.8 (multiple subdomains) + possibly M8145/3 (adenocarcinoma, diffuse)
	- non-endocrine pancreas carcinoma Stage IV - ICD C25.[012379] + metastasis code or C25.8 (multiple subdomains) + possibly M8971/3 (pancreas blastoma)
	- center-specific tumor entities
2.	Age ≥ 18 years
3.	Ability to understand written and verbal questions in German
4.	Willingness to participate in the study
5.	Informed consent
Exclusion criteria:	
1.	Other hemato-oncological disease (e.g. leukemia)
2.	Dementia
3.	Psychosis/delirium
4.	Major depression

### Outcome assessment

We will consider EPC to be feasible if 75 % of all eligible patients (i.e. adult patients diagnosed with an incurable, metastatic cancer [ICD 10 C 1–80 plus ICD 10 C 78–79]) are referred to a PC physician at their center at least once within eight weeks of the initial diagnosis.

Patients’ QoL and symptom burden will be assessed at the initial PC consultation using the “Palliative Outcome Scale” (POS) [16], the “European Organization for Research and Treatment of Cancer (EORTC) QLQ-C30” [17], and the “Hospital Anxiety and Depression Scale” (HADS) [18]. Both in the preliminary and the main study phase, a follow-up assessment will be conducted at 12 and 24 weeks using these three instruments. Family/caregivers of the patient will be asked to assess the patients’ situation by filling out the “Quality of Dying and Death” questionnaire [19].

The effects of EPC on healthcare costs will be measured in part by the number of follow-up visits a patient requires after the initial PC consultation, as recorded by the PC physician. In addition, patients will be asked to keep track of any additional costs in an expense log/cost diary. The expense log/cost diary is a bottom-up approach to understand direct and indirect costs of care from a patient perspective and a societal perspective. It will allow us to follow which kind of health-related services/treatments are used including services not reimbursed by the Statutory Health Insurance, how much productivity of patients and caregivers is lost and how much patients and their families spend on out-of-pocket payments. Accordingly, patients and their caregivers will be instructed to quantify all health-related costs and the reason for the costs in a provided expense log/cost diary. The expense log/cost diary will be developed based on a literature review and interviews with patients and their families. It will be pretested extensively before routine use.

### Quantitative data collection in the preliminary and main study phase

In each participating CCC, a study coordinator will be appointed. As soon as a patient is identified in the tumor board as a potential participant, the study coordinator will contact the patient, provide the patient with information and ask for the patient’s consent to participate in the study. If the patient is willing to participate, the study coordinator will explain the expense log/cost diary and hand it out to the patient. He will also ask the patient to fill out the T0-questionnaires. The T0-questionnaires (i.e. POS, EORTC, QLQ-C30 and HADS) will be added to the patient file and will therefore be accessible to the treating physician. After 12 weeks, the patient will be contacted again by the study coordinator and will be asked to complete the T1-questionnaires. At the same time, the study coordinator will remind the patient to regularly fill out the expense log. A second follow-up assessment will occur at 24 weeks, and the patient will be asked to complete the T2-questionnaires. Also, the patient will be asked to return the completed expense log.

The patient burden in the last days of life will be assessed externally by a family member or most relevant caregiver of the patient. After the patient’s death, the family member/caregiver will be contacted and asked to complete the “Quality of Dying and Death” questionnaire via telephone. If the patient has not died by the end of the study phase, this questionnaire will not be filled out.

The following figures show the course of events for both quantitative arms and the timeline for data collection for the quantitative and qualitative arms (Figs. 1 and 2).

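### The only described return of the expense log is by the patient at 24 weeks, so logs of patients who die or withdraw earlier are at risk and the secondary cost comparison may be biased towards 24-week survivors

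*Protocol article*

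**What the plan says.** The Protocol article, section Quantitative data collection in the preliminary and main study phase, traces the log from start to finish. The study coordinator explains it and hands it over once the patient agrees to take part. At 12 weeks the log is mentioned only as a prompt: "At the same time, the study coordinator will remind the patient to regularly fill out the expense log". The next contact is described as "A second follow-up assessment will occur at 24 weeks, and the patient will be asked to complete the T2-questionnaires", followed by "Also, the patient will be asked to return the completed expense log".

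The same section plans one contact for patients who die: "After the patient’s death, the family member/caregiver will be contacted and asked to complete the “Quality of Dying and Death” questionnaire via telephone". The log is not part of that call as described.

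The section Outcome assessment (quantitative arm) makes the log a shared task: "patients and their caregivers will be instructed to quantify all health-related costs and the reason for the costs in a provided expense log/cost diary". It assigns to the log the use of services (including those not reimbursed), lost productivity and out-of-pocket spending. The second cost measure is that costs are "measured in part by the number of follow-up visits a patient requires after the initial PC consultation, as recorded by the PC physician".

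The effect on healthcare costs is listed among the additional interests in Background and Discussion. The main goal is feasibility.

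**The concern.** Patients enter within eight weeks of a first diagnosis of metastatic, incurable cancer, in particular Stage IV lung, oesophageal, stomach and pancreatic tumours. Some will die before 24 weeks, and the post-death questionnaire shows that the authors expect deaths during the study. If the log comes back only from patients who reach the 24-week contact, the missing logs are determined by death and withdrawal, both of which are plausibly related to cost.

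Two consequences follow. First, the comparison would describe costs among 24-week survivors and would omit the last weeks of life of those who die earlier. Background reports that, in an earlier study in non-small cell lung cancer, early palliative care (EPC) "decreased the number of aggressive (and generally futile) therapies at the end of life", so part of any cost effect could fall in that period. Second, Background also reports longer survival with EPC in that study. If that happened here, the two phases would return logs from differently selected patients, and costs could differ for that reason alone.

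Logs that were never collected cannot be restored by analysis, so this has to be settled before data collection.

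**Working it through.** The article states no cost-endpoint sample size, mortality or dropout rate, so there is no figure of the plan to reproduce beyond 5 centres × 200 = 1000 patients per phase, which is consistent. All rates below are assumptions.

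**1. Collection points described**

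| Contact | Who | Log handling described |
|---|---|---|
| Consent / T0 | patient | handed out |
| 12 weeks (T1) | patient | reminder |
| 24 weeks (T2) | patient | return requested |
| After death | caregiver | none |
| Withdrawal | – | none |

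**2. Deaths before 24 weeks**

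24 weeks = 24 × 7 / 30.44 = 5.52 months. Under exponential survival from T0 with median m months, P(death before 24 weeks) = 1 − exp(−ln 2 × 5.52 / m).

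| Assumed median (months) | P(death before 24 weeks) | Per 1000 patients |
|---|---|---|
| 6 | 0.47 | about 470 |
| 9 | 0.35 | about 350 |
| 12 | 0.27 | about 270 |
| 18 | 0.19 | about 190 |
| 24 | 0.15 | about 150 |

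The last column is the number of logs at risk from death alone, if 1000 patients per phase enter. Withdrawals would add to it. Section Quantitative data analysis does not make clear whether 1000 is before or after the expected response of about 50%. If before, the counts halve.

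**3. Precision**

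If 10%, 30% or 50% of logs are lost, 900, 700 or 500 of 1000 per phase remain. Power for a difference of 0.20 SD (two-sided 0.05) is then 0.99, 0.96 or 0.89. Starting from 500 per phase, 450, 350 or 250 remain, with power 0.85, 0.75 or 0.61. Power is reduced, but bias is the main issue.

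**4. Bias, as an illustration**

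Let d be the proportion who die before 24 weeks and R the cost of those patients relative to survivors (survivors = 1). Suppose EPC cuts cost by 20% in those who die before 24 weeks and has no effect in survivors.

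- Control mean = (1 − d) + d × R
- Main-phase mean = (1 − d) + d × R × 0.8

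For d = 0.30 and R = 2: control 0.70 + 0.60 = 1.30; main phase 0.70 + 0.48 = 1.18; true change 1.18/1.30 − 1 = −9.2%.

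| d | R = 1.5 | R = 2 | R = 3 | Survivors' logs only |
|---|---|---|---|---|
| 0.10 | −2.9% | −3.6% | −5.0% | 0% |
| 0.30 | −7.8% | −9.2% | −11.2% | 0% |
| 0.50 | −12.0% | −13.3% | −15.0% | 0% |

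This is deliberately one-sided: the whole effect is placed in those who die early. It shows what a survivor-only analysis can miss, not what it will miss.

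**5. Sensitivity to survival**

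If median survival were 9 months in the preliminary phase and 12 months in the main phase, about 65% and 73% of patients would reach 24 weeks (1 − 0.35 and 1 − 0.27). The main-phase logs would then include about 8 patients per 100 enrolled whose preliminary-phase counterparts returned no log. The direction of the resulting cost bias cannot be known in advance.

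**6. Can the other cost measure replace the log?**

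Follow-up visits are counted after the first palliative care consultation. Section The design of the study offers that consultation routinely in the main phase, while the preliminary-phase patients represent the status quo. The article defines no matching count for them. The measure therefore describes use of the programme, not a cost difference between phases.

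**The case against.** A reader might infer that cost data are lost for everyone who dies or drops out before 24 weeks. The article does not say that. It describes the path of a patient who reaches 24 weeks and is silent on other logs. Caregivers are also instructed to complete the log and are contacted after a death, so a log may exist and be retrievable. The text is a condensed article, and retrieval may be set out in a fuller document or in the timeline figure, which is not shown. This stands, so the supported claim is risk of loss, not certain loss.

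A reader might also infer that the cost aim cannot be answered. That goes too far. The aim is secondary and modestly worded, visits are recorded independently of the log, and the Abstract lists economic burden among the interview topics. Interviews and visit counts can inform the aim, although neither gives a between-phase cost estimate.

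A third inference is that the cost effect lies at the end of life. No end-of-life cost endpoint is named. The support is one background finding in one tumour type, and out-of-pocket and productivity costs also arise in survivors.

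Finally, eligibility includes centre-specific tumour types, so survival may be longer than the shorter medians assumed. That is why the range runs to 24 months.

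What remains is that the article sets a collection schedule whose only return point is one that patients who have died cannot attend, and gives the one contact after death a different task.

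**Conclusion.** The concern holds as a risk of informative loss. As described, the log is returned only by the patient at 24 weeks. Logs of patients who die or withdraw earlier may not be recovered, and the secondary cost comparison would then be biased towards 24-week survivors and sensitive to any survival difference between phases.

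The share at risk from death is about 15% to 47%, resting wholly on assumed exponential survival with medians of 24 down to 6 months. Actual loss would be smaller if caregivers return logs and larger if withdrawals are added. The follow-up visit count does not close the gap, because it has no defined control-phase counterpart. The main feasibility result, which uses centre records, is not affected. The change should be made, because it is cheap and cannot be made after the data are collected.

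**What to change.** - At the existing 12-week contact, collect the completed part of the log and issue a new one.
- At the existing caregiver call after death, ask for the remaining log up to death. At withdrawal, ask the patient for it.
- Analyse costs from T0 to death or 24 weeks, including every patient who contributed a log. Report by phase how many logs were returned and the period each covers.
- Report EPC follow-up visits as a programme cost of the main phase, not as a measure of the effect on costs.

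The cost is a second copy of the log, one more item at contacts that already take place, some data entry, and a small added burden on bereaved caregivers. Patients who return no log at all will still be missing, so the change reduces the bias without removing it.
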